From this population of midlife and older adults, we will also focus on recruiting individuals who are low-income and experience mobility impairments. We selected this focus as these are two problems that co-occur with aging [41, 67] yet are minimally studied [68–70]. Furthermore, there is an unmet need for health care for individuals who are both low-income [71–73] and have mobility impairments [71–73]. There is increasing scientific evidence supporting the use of telehealth in sleep and circadian medicine [74–76]. Therefore, the current study will deliver the MSI via telehealth to increase accessibility for this underserved population.

In summary, the overarching goal of the current study is to assess whether memory support strategies implemented into TranS-C can improve patient memory for treatment thereby improving patient outcomes among midlife and older adults. Over a 4-year period, midlife and older adults (*n* = 178, including 20% for attrition) will be randomly allocated to TranS-C + MSI or TranS-C alone and will be assessed at pre-treatment, post-treatment, 6-month follow-up (6FU), and 12-month follow-up (12FU). This is a randomized control trial that incorporates aspects of both Stages 2 and 3 of the NIH Stage Model [77]. Specifically, therapists affiliated with the research team will deliver the intervention to maintain the high level of control necessary to establish fidelity and internal validity (Stage 2). Participants will be recruited from community settings as a first step toward testing the delivery of the MSI in routine practice (Stage 3), bridging the gap between research and practice [78, 79].

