#### Sample size {14}

For Aim 1, sample size was determined by conducting a power analysis using Optimal Design [139, 140] for person-randomized, repeated measures trials with four timepoints (pre-treatment, post-treatment, 6FU, and 12FU). Using a prior dataset comparing CT + MSI and CT-as-usual for depression [25] (R01MH108657), the effect size was calculated for midlife and older adults (≥ 50 years) by averaging the effect size for depression severity at post and 6FU. This approach yielded an effect size of* d* = 0.50. To achieve 80% power, 146 participants are needed. Adding 20% for attrition results in a sample size of 176. For Aim 2, Fritz and MacKinnon [141] provide recommendations for mediation sample size. Using data from R01MH108657 for midlife and older adults (≥ 50 years), the path from the predictor (average constructive memory support) to the mediator (recall at mid-treatment) was small to medium (*f* = 0.18) and the path from the mediator (recall at mid-treatment) to outcome (functional impairment at post-treatment) was medium (*f* = 0.23). Based on these estimates, a sample size of 148 is needed. Adding an additional 20% for attrition results in a sample of 178. The powerMediation package in R [142] was used to calculate the minimum detectable indirect effect of average constructive memory support on outcomes at 6FU and 12FU via recall at mid-treatment. With the proposed sample size of 178 needed for mediation at post-treatment, a minimum standardized indirect effect of 0.56 for outcomes at 6FU and 0.66 for outcomes at 12FU can be detected. The present study focused on powering the primary timepoint of interest, post-treatment. As treatment effects tend to decline over time, we may not be adequately powered to detect statistical significance at 6FU and 12FU. Thus, effect sizes, rather than statistical significance, will be emphasized for the follow-up timepoints. For Aim 3, a minimum detectable effect size difference was calculated via PowerUp! [143]. Estimates from pre-treatment to post-treatment impairment were generated from two prior datasets: (1) midlife and older adults (≥ 50 years), who were randomized to CT + MSI and CT-as-usual [25] (R01MH108657) and (2) midlife and older adults (≥ 50 years), who participated in the pilot trial of TranS-C + MSI [24]. The moderator with the smallest estimates (education from the R01MH108657 trial) was used to help ensure adequate sample size. With an alpha of 0.05, 80% power, and a sample size of 178 (calculated for Aim 2 mediation), the MDES for the moderator effect was *d* = 0.24. Considering that this effect size is comparable to the effect size yielded by similar analyses using prior data (*d* = 0.25 in the R01MH108657 trial), the sample size calculated for Aim 2 will be sufficient to power Aim 3. Together, a minimum sample size of 178 will be sufficient to power all three aims.

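### The attrition allowance multiplies by 1.2 instead of dividing by 0.8, so the 178 enrolled cover about 17% loss, not the stated 20%

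*Protocol article*

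**What the plan says.** In the protocol article, Sample size {14}, the Aim 1 requirement is "To achieve 80% power, 146 participants are needed", followed by "Adding 20% for attrition results in a sample size of 176". The Aim 2 (mediation) requirement is "Based on these estimates, a sample size of 148 is needed", followed by "Adding an additional 20% for attrition results in a sample of 178". The larger figure becomes the enrolment target, and the section closes with "Together, a minimum sample size of 178 will be sufficient to power all three aims".

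Background and rationale {6a} gives the number to be randomised as 178 and describes it as "including 20% for attrition".

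**The concern.** Attrition is a share of the people enrolled. To have a required number left after losing a fraction *d* of enrolment, one enrols the requirement divided by (1 − *d*). Adding *d* times the requirement gives a smaller number, and losing a fraction *d* of that number leaves fewer than were needed.

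Both stated totals look like the second calculation. If so, a reader who relies on the article will believe that 20% loss still leaves the 146 and 148 that the power work calls for, when it does not. At stake is whether a stated property of the sample size is true. The design and the analysis are not in question.

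**Working it through.** **Inputs**, all from the protocol article: requirement before attrition 146 (Aim 1) and 148 (Aim 2); allowance 20%; stated totals 176 and 178; power 80% at 146 for Aim 1 (Sample size {14}); alpha 0.05 (Statistical methods). Sidedness is not stated, and two-sided is assumed here. The 146 and 148 are taken as given.

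**Step 1: reproduce the stated totals.** Requirement × 1.2:
- Aim 1: 146 × 1.2 = 175.2, rounded up to 176.
- Aim 2: 148 × 1.2 = 177.6, rounded up to 178.

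Both match exactly.

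**Step 2: the calculation that protects against 20% loss.** Requirement ÷ (1 − 0.20):
- Aim 1: 146 / 0.8 = 182.5, rounded up to 183.
- Aim 2: 148 / 0.8 = 185.

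Neither matches the stated totals, so the method used is the multiplication. Covering both aims at 20% loss would take 185 enrolled, which is 185 − 178 = 7 more.

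**Step 3: what 178 leaves at 20% loss.** 178 × 0.8 = 142.4, about 142.
- Aim 1: 146 − 142 = 4 short.
- Aim 2: 148 − 142 = 6 short.

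**Step 4: the loss that 178 does cover.**
- Keeping 148: 1 − 148/178 = 0.169, or 16.9%.
- Keeping 146: 1 − 146/178 = 0.180, or 18.0%.

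Put another way, the margin built in is 178 − 148 = 30 people, whereas 20% of 178 is 35.6.

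**Step 5: approximate Aim 1 power at 142.** If 146 gives 80% power at two-sided 0.05, the standardised effect at 146 is 1.96 + 0.84 = 2.80. It scales with the square root of the number evaluable:
- 2.80 × √(142/146) − 1.96 = 0.80
- Φ(0.80) = 0.79, so about 79%.

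This is a rescaling from the plan's own 80% point. It is not a rerun of the repeated-measures calculation, whose variance inputs the article does not give. No equivalent figure is offered for Aim 2, because the same scaling is not a mediation power calculation.

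**The case against.** **The wording is a literal top-up.** The text speaks of adding 20%, and as a 20% increase the sums are right. Nowhere does the article say in so many words that 20% of enrolled participants are expected to be lost. This explains how the figure arose, but it does not rescue the claim. The increase is made for attrition, the Background section describes the enrolled 178 as "including 20% for attrition", and the sufficiency statement carries no qualification. A reader will take 20% loss as covered.

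**Dropouts still contribute data.** Under the missing-data section {20c}, all randomised participants are analysed, and the hierarchical and structural equation models use all available data by maximum likelihood. Participants who stop treatment are still approached for assessments ({18b}, {20c}). Someone lost after post-treatment, the timepoint for which the trial is powered, still counts there. This stands: 142 is a head-count worst case. It does not remove the point, for two reasons. The sample size section makes its own allowance by head count. And randomisation follows the pre-treatment assessment ({18a}), so a person lost before post-treatment may bring only baseline and perhaps mid-treatment memory data, which add little to a post-treatment contrast on the outcomes.

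**The size is small.** This also stands: 4 to 6 people, and about one point of power for Aim 1.

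**A stronger reading that does not hold.** A reader might infer that every power figure in the section is wrong. The 80% at 146 and the requirement of 148 come before the inflation step. The minimum detectable indirect effects of 0.56 (6 months) and 0.66 (12 months) and the Aim 3 detectable effect of 0.24 are computed at 178 itself; for Aim 3 the text reads "With an alpha of 0.05, 80% power, and a sample size of 178". They would be the same however 178 had been reached. Whether they ought to be quoted at a post-attrition number is a separate question.

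**Conclusion.** Wrong as written, with a small effect. The totals 176 and 178 come from multiplying by 1.2, and 178 does not deliver the 20% allowance attributed to it. It keeps 148 evaluable up to 16.9% attrition and 146 up to 18.0%. Only the two totals and the statements resting on them (the 20% allowance and the sufficiency for all three aims) are affected.

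The arithmetic needs no assumption beyond reading 20% as a share of those enrolled. The Aim 1 power of about 79% at 142 further assumes a two-sided test, a normal approximation anchored at the stated 80% for 146, and that lost participants contribute nothing. Partial data would reduce the loss. The documents do not support a conclusion that the trial is materially underpowered because of this slip.

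**What to change.** Keep 178 and correct what is said about it.

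- **Sample size {14}:** state that 178 allows for 16.9% attrition for the 148 evaluable participants of Aim 2, and 18.0% for the 146 of Aim 1. Add that at 20% attrition about 142 would be evaluable by head count, with Aim 1 power of approximately 79%, labelled as an approximation. Word the closing sufficiency statement so that it applies up to those attrition levels. Correct or remove the intermediate 176, which on its own keeps 146 only up to 1 − 146/176 = 17.0% loss.
- **Background and rationale {6a}:** replace the 20% description of the 178 with the matching figure.

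The cost is about a sentence in each of two places, and a slightly less favourable stated allowance. Recruitment, design and analysis do not change, and the detectable effects quoted at 178 need no revision on this account.

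### The 6FU and 12FU figures of 0.56 and 0.66 cannot be minimum detectable standardised indirect effects at N = 178 given the plan's own 0.18 path; recalculate or relabel them

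*Protocol article*

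**What the plan says.** Sample size {14} handles mediation in two steps.

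- **Post-treatment.** The path from average constructive memory support to mid-treatment recall is put at *f* = 0.18. The path from that recall to functional impairment at post-treatment is put at *f* = 0.23. The section continues: "Based on these estimates, a sample size of 148 is needed". A 20% attrition allowance then raises this to 178.
- **Follow-up.** An R package, powerMediation, "was used to calculate the minimum detectable indirect effect of average constructive memory support on outcomes at 6FU and 12FU via recall at mid-treatment". Taking the 178 enrolled as the number available, the section reports that "a minimum standardized indirect effect of 0.56 for outcomes at 6FU and 0.66 for outcomes at 12FU can be detected".

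For the follow-up step the section gives no power, sidedness, standard deviations or predictor-mediator correlation. It then concedes that significance at 6FU and 12FU may be out of reach because effects tend to fade, and says effect sizes will be emphasised there.

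**The concern.** Both steps use the same predictor and the same mid-treatment mediator, and both refer to 178 people. The first path is therefore the same quantity whichever outcome time is considered. On a fully standardised scale, the detectable second path depends only on the number analysed, the predictor-mediator correlation and the residual variance. Changing the outcome time does not by itself move the detectable product from hundredths to more than one half.

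Objectives {7} hypothesises mediation at both follow-ups, and these two numbers are the only follow-up benchmarks offered for it. Taken literally, they say that no realistic mediation effect could be detected at 6FU or 12FU. With a first path of 0.18 and no direct effect, the second path is a correlation and cannot exceed 1, so the indirect effect cannot exceed 0.18. A reader who relies on the figures would misjudge what a null or positive mediation result at follow-up can show.

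**Working it through.** **Inputs from Sample size {14}:** N = 178; 148 before attrition; a 20% allowance; first path 0.18; stated minima 0.56 and 0.66. **From Statistical methods:** alpha = 0.05. **Assumed:** two-sided test, 80% power (stated for Aims 1 and 3, not for this step), standardised variables, and no direct effect in the equal-path calculations. The multiplier is 1.960 + 0.842 = 2.802.

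**1. The plan's own figures.** 148 × 1.2 = 177.6, which rounds up to 178, so the enrolment figure reproduces. The 0.56 and 0.66 did not reproduce as standardised indirect effects under any setting tried: one- or two-sided, 80% or 90% power, n = 178, 148 or 142, and predictor-mediator correlation from 0 to 0.5.

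**2. Smallest detectable mediator slope.** b = 2.802 × (SD of residual / SD of mediator) / √(n(1 − ρ²)).

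On the standardised scale the residual SD is at most 1, so with ρ = 0.18 and n = 178:

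b ≤ 2.802 / √(178 × 0.9676) = 2.802 / 13.124 = 0.213.

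Multiplied by the first path: 0.18 × 0.213 = 0.038. If *f* is read as f-squared instead, the first path becomes √(0.18/1.18) = 0.39, the slope 0.228 and the product 0.089.

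**3. Smallest detectable product with equal paths (r each).**

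- Joint significance: solve Φ(r√n/√(1 − r²) − 1.96) × Φ(r√n − 1.96) = 0.80. At n = 178, r = 0.237 and r² = 0.056 (0.057 with degrees-of-freedom corrections).
- Sobel: r√n/√(2 − r²) = 2.802, so r² = 2 × 7.849/(n + 7.849). At n = 178 this is 15.698/185.849 = 0.084.

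**4. At the number likely to be assessed.** 178 × 0.8 = 142.4, so about 142; 148 is the plan's own pre-attrition number.

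| n | slope (ρ = 0.18) | × 0.18 | equal paths, joint | equal paths, Sobel |
|---|---|---|---|---|
| 178 | 0.213 | 0.038 | 0.056 | 0.084 |
| 148 | 0.234 | 0.042 | 0.067 | 0.101 |
| 142 | 0.239 | 0.043 | 0.070 | 0.105 |

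**5. What would make the stated figures true.**

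- As a standardised slope at n = 178, ρ = √(1 − (2.802/0.56)²/178) = 0.93 for 0.56, and 0.95 for 0.66. The plan's path is 0.18.
- As a standardised slope at ρ = 0.18, the number analysed would be about 26 for 0.56 and 19 for 0.66.
- Raising power does not help. At 99% power the multiplier is 4.286 and the slope is 0.327 at n = 178 or 0.366 at n = 142.
- As an indirect effect with the first path at 0.18, the second path would be 0.56/0.18 = 3.1 or 0.66/0.18 = 3.7.
- As a slope in unstandardised units, the residual-to-mediator SD ratio would be 0.56/0.2135 = 2.6 at 6FU and 0.66/0.2135 = 3.1 at 12FU. This is possible, but the article reports no SDs against which to check it.

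**The case against.** The best defence is that the arithmetic may be sound and only the label wrong. If the software returned a mediator slope in raw or partly standardised units, SD ratios of 2.6 and 3.1 would produce exactly these figures. A condensed article need not print every input. That possibility stands, and it is why relabelling is an acceptable remedy. It does not rescue the sentence as printed, which names both the scale and the quantity.

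Second, the section already admits low power at follow-up, and the two figures set neither the sample size nor a decision rule. This limits the consequence. The admission, however, concerns true effects that shrink over time. It does not cover a detection threshold stated on the wrong scale, and it leaves readers with effect sizes as the yardstick.

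Three stronger readings may tempt a reader, and the documents do not support them.

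- **That the figures contradict the plan's path estimates**, whose product is 0.18 × 0.23 = 0.041. A detectable minimum above an expected effect signals low power, not inconsistency, and the 0.23 path is for post-treatment only. The sound comparison is with what 178 people can detect.
- **That they exceed the whole treatment effect of d = 0.50.** That effect is an arm contrast obtained by "averaging the effect size for depression severity at post and 6FU". The mediation figures take amount of memory support as predictor and use another outcome and metric. An indirect effect can also exceed a total effect when the direct effect runs the other way.
- **That they are wrong by a factor of ten.** The ratio is about 2.6 (6FU) and 3.1 (12FU) against the standardised slope, and up to about 16 against the expected product (0.66/0.0414). It is near ten only against the equal-path joint-significance product.

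**Conclusion.** The point holds as an error of label, scale or inputs. At N = 178 and with the plan's path of 0.18, the detectable standardised indirect effect is in the region of 0.04 to 0.08, and the detectable standardised slope is at most about 0.21. The stated 0.56 and 0.66 are neither. Whether they are miscalculated or are correct values of another quantity cannot be settled from the article.

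The result rests on the assumed two-sided 5% test and 80% power and on reading *f* = 0.18 as approximately a correlation. The conclusion survives 90% and 99% power, a one-sided test, the smaller numbers assessed, and the f-squared reading. It would fail only if predictor and mediator were nearly collinear, which the stated path rules out.

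The consequence is moderate. The figures concern the follow-up times of a secondary aim, and enrolment does not depend on them. Whether 148 is adequate for post-treatment mediation is a separate question, not judged here.

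**What to change.** Do one of the following in Sample size {14}:

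- Recalculate the 6FU and 12FU minimum detectable indirect effects on a named scale, at the number expected to be assessed rather than the 178 enrolled. State alpha, power, the test and the assumed paths. Under equal paths at 142 to 148 assessed, the values would be about 0.07 (joint significance) to 0.10 (Sobel).
- Keep 0.56 and 0.66 but call them what the software returned, for example a mediator slope. Give the units, the residual and mediator SDs, the predictor-mediator correlation, alpha and power.

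The cost is one recalculation and a reworded sentence. Sample size and trial conduct are unaffected.

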### Objectives {7}

The first aim is to assess the efficacy of incorporating the MSI into TranS-C, compared to TranS-C alone. We hypothesize that compared to TranS-C alone, TranS-C + MSI will be associated with improvements in sleep and circadian functioning, daytime functioning, well-being, and patient memory at post-treatment, 6FU, and 12FU. The second aim is to evaluate if patient memory for treatment contents mediates the relationship between treatment condition and sleep and circadian functioning. We hypothesize that TranS-C + MSI will be associated with enhanced memory for treatment relative to TranS-C alone and enhanced memory for treatment will be associated with improvements in sleep and circadian functioning at post-treatment, 6FU, and 12FU. The third aim is to assess whether previously reported poor treatment response sub-groups will moderate the relationship between treatment condition and (a) patient memory for treatment and (b) treatment outcome, such that individuals in these sub-groups may derive a greater benefit from receiving memory support. It is hypothesized that treatment effects for those in the TranS-C + MSI condition will be larger at post-treatment for individuals who are older, have fewer years of education, poorer baseline cognitive functioning, and more severe baseline sleep disruption and sleep-related impairment. Exploratory analyses will compare treatment condition on (a) patient adherence, patient-rated treatment credibility, and patient utilization of treatment contents and (b) therapist-rated acceptability, appropriateness, and feasibility.

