### Participant measures

Across participant measures, the post-treatment time point is of primary interest.

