## Statistical methods

An alpha = 0.05 will be used for each primary hypothesis. The Benjamini–Hochberg procedure [145] will be used to correct for multiple testing for confirmatory analyses on the primary outcomes (i.e., PROMIS-SD, SDS, SWLS).

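### Benefits hypothesised at 6FU and 12FU are to be read mainly from effect sizes with no precision attached, and the Aim 1 interaction rule can remove those same estimates

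*Protocol article*

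**What the plan says.** Only the protocol article is at hand. Five places bear on this point.

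- **Objectives {7}.** Aim 1 hypothesises "improvements in sleep and circadian functioning, daytime functioning, well-being, and patient memory at post-treatment, 6FU, and 12FU". Aim 2 hypothesises that "enhanced memory for treatment will be associated with improvements in sleep and circadian functioning at post-treatment, 6FU, and 12FU". The follow-up parts are not labelled exploratory. That label is kept for adherence, credibility, utilization and the therapist ratings.
- **Participant measures.** Across participant measures, "the post-treatment time point is of primary interest". Sample size {14} likewise says that powering concentrated on post-treatment.
- **Sample size {14}.** Because effects tend to fade, "we may not be adequately powered to detect statistical significance at 6FU and 12FU". The next sentence draws the consequence: "Thus, effect sizes, rather than statistical significance, will be emphasized for the follow-up timepoints".
- **Statistical methods (opening).** "An alpha = 0.05 will be used for each primary hypothesis", with Benjamini-Hochberg used to "correct for multiple testing for confirmatory analyses on the primary outcomes (i.e., PROMIS-SD, SDS, SWLS"). Neither statement names time points.
- **Statistical methods {20a}.** In the Aim 1 model, treatment-by-time interactions stay only if significant at 5%, and significant ones are followed by planned contrasts. Aim 2 specifies separate mediation models for PROMIS-SD and PROMIS-SRI at post-treatment, 6FU and 12FU.

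**The concern.** The follow-up parts of Aims 1 and 2 are hypotheses, so the report will have to say whether they were supported. For those parts the protocol states that significance will carry less weight because power may be low, and it names nothing in its place that shows how precise the estimate is. Low power and low precision are the same condition, so a point estimate on its own is least informative exactly where the plan means to lean on it.

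There is also an internal conflict. The Aim 1 model lets a 5% test decide whether there are visit-specific treatment effects at all, whereas the sample size section wants visit-specific effect sizes emphasised irrespective of significance. An analyst cannot fully follow both.

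At stake is what can be said about lasting benefit at 6 and 12 months. The post-treatment conclusions are not affected.

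**Working it through.** **1. Inputs**

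- Randomised: 178, allocated 1:1 (Sample size {14}, Trial design {8}).
- Attrition: 20% (Sample size {14}). The stated total follows as 148 × 1.2 = 177.6, rounded up to 178.
- Assessed at follow-up: 178 × 0.8 = 142.4, taken as 142. This is my assumption, and I vary it below.
- The article gives no precision figure for Aim 1 contrasts at 6FU or 12FU, so there is none to reproduce. (The Aim 1 figure of 146 comes from repeated-measures software whose variance inputs are not given, and nothing here depends on it.)

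**2. Precision of a follow-up contrast**

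For two equal arms at one visit, SE(d) ≈ √(4/N).

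- N = 142: SE = √(4/142) = 0.168; half-width = 1.96 × 0.168 = 0.33.
- Observed d = 0.20: 0.20 ± 0.33, or about -0.13 to 0.53.
- N = 178 (no loss): half-width 0.29. N = 106: half-width 0.38.

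The modelled contrast is a difference in change from pre-treatment. Its SE is the one above times √(2(1 − r)), where r is the correlation between visits. At r = 0.5 the factor is 1. At r = 0.7 it is √0.6 = 0.775, giving a half-width of 0.329 × 0.775 = 0.255, so d = 0.20 still has an interval that includes zero (both values of r are assumptions).

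**3. Power if the effect fades as the protocol expects** (two-sided 5%, single visit, N = 142)

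| True d | Power |
|---|---|
| 0.5 | 0.85 |
| 0.4 | 0.66 |
| 0.3 | 0.43 |
| 0.2 | 0.22 |

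The protocol's caution is therefore apt if the effect declines, and unnecessary if d stays at the planning value of 0.50.

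**4. Illustration under an assumed threshold**

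The protocol sets no effect-size bar. Suppose a reader treated a favourable d of 0.20 or more as a small effect. With no true effect:

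- One contrast: 1 − Φ(0.20/0.168) = 0.117 (0.15 at N = 106, 0.09 at N = 178).
- At least one of six (three primary outcomes × two follow-ups): 0.42, 0.36 and 0.29 at assumed common correlations of 0.3, 0.5 and 0.7.
- At a bar of 0.30, one contrast: 0.037.

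These figures describe the assumed bar, applied with no other safeguard. They are not error rates of this protocol.

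**5. What the other rules cover**

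- *Interaction test, Aim 1.* If the interactions are judged together, a post-treatment difference can keep the 6FU and 12FU terms in the model. If they are judged term by term, only significant follow-up terms survive, which is the opposite of playing significance down. If all are dropped, what remains is a single treatment coefficient common to all visits, with no 6FU or 12FU effect size left to emphasise.
- *Benjamini-Hochberg.* It names three outcomes and no time points. How it would work at visits where significance is not the emphasis is not said.
- *Aim 2.* The interaction rule belongs to the Aim 1 model, and the Benjamini-Hochberg text does not mention indirect effects. The article states minimum detectable indirect effects of 0.56 (6FU) and 0.66 (12FU). The product of its two planning paths is 0.18 × 0.23 = 0.04. The scales may differ, so this comparison is only indicative, but it suggests that follow-up mediation is where precision is poorest.

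**The case against.** The strongest reply is that emphasising estimates at secondary, possibly underpowered time points is sound practice, because it avoids reading non-significance as absence of effect. The sentence does not drop tests, forbid intervals or say that an estimate above some size counts as support. The protocol also discloses the power limit in advance and makes post-treatment primary, and a missing mention of confidence intervals could be detail left to the analysis plan.

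Much of this stands. It confines the point to follow-up claims and rules out several stronger readings that a reader might infer:

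- *That the plan lacks power at follow-up.* The text says only that power may be inadequate, and at an undiminished d of 0.50 it would be about 85% with 142 assessed.
- *That a small effect size is the written criterion for success.* No threshold is written, so the chance figures in step 4 are illustrations.
- *That follow-up has no error control.* The 5% interaction test and Benjamini-Hochberg give some for Aim 1.
- *That the emphasis is wrong because it selects inflated estimates.* For a true d of 0.10 to 0.20, estimates of 0.20 or more average 0.30 to 0.33, but estimates whose interval excludes zero (0.329 or more) average 0.41 to 0.43. Selecting on significance inflates more, so this argument does not help.

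What the reply does not remove is that this is more than silence. The protocol states an interpretive rule for hypothesised effects, ties it to low power, and elsewhere states a modelling rule that conflicts with it.

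**Conclusion.** The point holds in a limited form. For effects that the Objectives hypothesise at 6FU and 12FU, the protocol moves the emphasis from significance to effect size without attaching any measure of precision. With about 142 assessed, the 95% interval for d is roughly ±0.33 (0.29 to 0.38 for 178 down to 106 assessed), so an estimate of 0.20 is compatible with no effect and is not support on its own. The existing safeguards are partial for Aim 1 and are not stated to reach the Aim 2 follow-up models. The rule that drops non-significant interactions works against the stated emphasis.

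The size rests on two equal arms, a single-visit standard error and 20% loss by follow-up. The post-treatment analysis is unaffected.

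**What to change.** Replace the sentence in Sample size {14} with wording such as:

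> Post-treatment is the confirmatory time point. Treatment contrasts (Aim 1) and indirect effects (Aim 2) at 6FU and 12FU are secondary, are estimated whatever the result of the interaction test, and are reported as effect sizes with 95% confidence intervals. An effect whose interval includes zero is described as inconclusive and is not claimed as support, whatever its size.

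Then align three places: mark the 6FU and 12FU parts of the hypotheses in Objectives {7} as secondary; state in Statistical methods that the Benjamini-Hochberg step applies to the post-treatment contrasts on PROMIS-SD, SDS and SWLS; and remove the condition in the Aim 1 text of {20a} that non-significant interactions are dropped.

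This keeps the emphasis on estimates. The intervals are unadjusted, which suits secondary results but should be said plainly: with no true effect, at least one of the six follow-up intervals on the primary outcomes would exclude zero in favour of MSI with probability of about 0.08 to 0.12 (assumed correlations 0.7 to 0.3).

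The cost is a few sentences and no new data, and recruitment is stated to run through October 2026. The downside is that follow-up claims become more cautious.
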